## Abstract

**Background:**

Cardiac rehabilitation (CR) is a secondary prevention program that offers education and support to assist patients with coronary heart disease (CHD) make lifestyle changes. Despite the benefits of CR, attendance at centre-based sessions remains low. Mobile technology (mHealth) has potential to reach more patients by delivering CR directly to mobile phones, thus providing an alternative to centre-based CR. The aim of this trial is to evaluate if a mHealth comprehensive CR program can improve adherence to healthy lifestyle behaviours (for example, physically active, fruit and vegetable intake, not smoking, low alcohol consumption) over and above usual CR services in New Zealand adults diagnosed with CHD.

**Methods/design:**

A two-arm, parallel, randomised controlled trial will be conducted at two Auckland hospitals in New Zealand. One hundred twenty participants will be randomised to receive a 24-week evidence- and theory-based personalised text message program and access to a supporting website in addition to usual CR care or usual CR care alone (control). The primary outcome is the proportion of participants adhering to healthy behaviours at 6 months, measured using a composite health behaviour score. Secondary outcomes include overall cardiovascular disease risk, body composition, illness perceptions, self-efficacy, hospital anxiety/depression and medication adherence.

**Discussion:**

This study is one of the first to examine an mHealth-delivered comprehensive CR program. Strengths of the trial include quality research design and in-depth description of the intervention to aid replication. If effective, the trial has potential to augment standard CR practices and to be used as a model for other disease prevention or self-management programs.

**Trial registry:**

Australian New Zealand Clinical Trials Registry:
ACTRN12613000901707

## Background

Unhealthy lifestyle behaviours, including smoking, physical inactivity, hazardous alcohol consumption and low intake of fruit and vegetables have been shown to contribute to the development of coronary heart disease (CHD)
[1,2], which remains a leading cause of death worldwide
[3]. Lifestyle modifications are encouraged for secondary prevention of CHD. Cardiac rehabilitation (CR) is a cost-effective program of education and support designed to assist patients make healthy lifestyle changes and adhere to clinical guidelines, and it is associated with reduced mortality and hospitalisations
[4-7]. Recommended lifestyle changes can include starting and maintaining regular exercise, eating a heart-healthy diet, stopping smoking, adhering to prescribed medication regimens and attending medical appointments
[8-10].

Inviting patients hospitalised for CHD to attend centre-based CR is usual care in most developed countries, including New Zealand, yet attendance rates remain low
[11-13]. Barriers to attending CR include limited transportation and parking availability, inconvenient scheduling of CR sessions, language-related communication difficulties and employment or family demands
[14-16]. Alternative delivery methods of CR are required to better meet patients’ needs.

Delivering CR using mobile technologies, known as mHealth, has the potential to overcome such barriers, as programs can be personalised and delivered anywhere and at any time. mHealth interventions have successfully been shown to have a positive effect on health behaviours, such as smoking cessation and improvement in disease self-management
[17,18]; however, mHealth in a CHD population has not been thoroughly investigated to date. The recently completed Heart Exercise and Remote Technologies (HEART) trial (*N* = 171) demonstrated that a simple text message and Internet intervention was effective in general as well as cost-effective for increasing leisure time physical activity and walking, but not for increasing maximal oxygen uptake in people with CHD at 6 months after randomisation
[19,20]. Moreover, qualitative data indicated that the HEART intervention was well-received, had positive effects on participants’ physical activity levels and was not considered burdensome
[21]. Whilst HEART demonstrated the feasibility and effectiveness of implementing a mobile telephone intervention, it focused on only a single behaviour (exercise)
[22]. To build on this work, we propose testing the effectiveness of a comprehensive mHealth self-management intervention to enhance patients’ lifestyles.

Previous studies in which investigators targeted multiple risk factors often measured only one behaviour rather than the overall effect of the intervention
[23]. Evaluating the combined effect of the intervention to change multiple behaviours is important, as many CHD patients have more than one lifestyle-related risk factor. The primary aim of our present trial (Text4Heart) is to evaluate the effectiveness of a comprehensive mHealth CR program in improving adherence to recommended lifestyle behaviour guidelines at 6 months after randomisation, in addition to usual CR care. Secondary objectives include the effect of 6 months of the intervention on overall cardiovascular (CVD) risk, body composition, illness perceptions, medication adherence, self-efficacy and hospital anxiety and/or depression.

## Methods/design

This protocol describes a six-month, two-arm, parallel, randomised controlled trial to evaluate an mHealth-delivered comprehensive (that is, multiple health behaviour) CR intervention in adults with CHD on the basis of a composite health behaviour score. The protocol is in accord with the SPIRIT 2013 statement
[24], and the intervention is described according to the CONSORT-EHEALTH checklist
[25]. See Additional file
1 for the complete checklist.

### Study sample and recruitment

Eligible participants are English-speaking New Zealand adults (ages 18 years and older) with a documented diagnosis of CHD (myocardial infarction (MI), angina or revascularisation) who meet the criteria for usual CR care and have access to the Internet (for example, library, work or home access). A basic mobile telephone with which to receive text messages will be available on loan to participants who do not own one (fewer than one in ten New Zealanders). Exclusion criteria are untreated ventricular tachycardia, severe heart failure, life-threatening coexisting disease with life expectancy less than 1 year, and/or significant exercise limitations for reasons other than CHD.

Potential participants will be screened during hospital admission at two metropolitan hospitals in Auckland, New Zealand. The annual incidence of hospitalisation for CHD in New Zealand overall is approximately 162 people per 100,000
[26] and over 2,400 in the Auckland area. The recruitment strategy was effective in the HEART trial
[20,21]. Potential participants will receive a study information sheet while in hospital, and informed consent will be obtained from participants at the baseline assessment. All patients will be offered usual CR care. Assessments will be conducted in hospital, community clinics or participants’ homes to encourage retention.

### Outcome assessments

Assessments will be conducted at baseline and 6 months postrandomisation (see Figure 
1). Baseline assessments will involve an explanation of study procedures, signed consent and collection of demographic details. Participant-reported primary and secondary outcomes will then be collected, followed by physical measurements, including height, weight, waist and hip circumference, blood pressure and blood cholesterol. The baseline assessment concludes with randomisation and assignment of participants to the respective study groups.

**Figure 1 F1:**
[figure not shown]
**Flow diagram of the study protocol.** AUDIT C: Alcohol Use Disorders Identification Test alcohol consumption questions; Brief IPQ: Brief Illness Perception Questionnaire; CHD: Coronary heart disease; CR: Cardiac rehabilitation; GLTPAQ: Godin Leisure Time Physical Activity Questionnaire; HADS: Hospital Anxiety and Depression Scale; MMAS: Morisky 8-item Medication Adherence Scale.

### Ethical approval

Ethical approval was obtained from the Health and Disability Ethics Committee (13/NTA/6). Each hospital research committee also approved the study. Serious adverse events will be collected at 12 weeks and 6 months and will be reported to the ethics committees along with any protocol amendments or violations.

### Sample size

One hundred twenty participants (sixty per group) will provide at least 80% power at the 5% level of significance (two-sided) to detect an absolute difference of 25% between the two groups, in the proportions of participants adherent to recommended healthy behaviour guidelines (that is, not smoking, low alcohol consumption, fruit and vegetable intake and engaging in physical activity) at 6 months after randomisation.

The sample size calculation was based on data from the EPIC-Norfolk Prospective Population Study, in which the investigators used a composite health behaviour score to determine the relationship between lifestyle and total mortality by cause in adults between 45 and 79 years of age living in the general community
[27]. Given our population of people with established CHD, we estimate that 30% to 40% of our sample will be adherent to healthy behaviour guidelines at baseline
[27].

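### The stated power of at least 80% has no reserve: 120 is the number randomised, and 60 analysed per arm gives only about 80%

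*Protocol article*

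**What the plan says.** The Sample size section gives the claim: "One hundred twenty participants (sixty per group) will provide at least 80% power at the 5% level of significance (two-sided"). The effect is given as "to detect an absolute difference of 25% between the two groups" in the proportion adherent at 6 months after randomisation. The only rate offered is in the same section: "we estimate that 30% to 40% of our sample will be adherent to healthy behaviour guidelines at baseline".

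The Abstract (Methods/design) fixes what the 120 counts: "One hundred twenty participants will be randomised". Allocation is 1:1 (Randomisation and blinding). The main test is a simple chi-square comparison of proportions at the end of the intervention period, under intention to treat (Statistical analyses).

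The article states no rate of loss to follow-up. It mentions retention only in Study sample and recruitment: "Assessments will be conducted in hospital, community clinics or participants’ homes to encourage retention".

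**The concern.** The same 120 serves as the number randomised and as the number that yields the power. Both can be true only if practically everyone randomised provides a 6-month outcome. The wording "will provide at least 80% power" presents 80% as a floor, whereas the design reaches it only as a ceiling, under full follow-up.

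The stake is how the result is read. A null result would be taken to come from a trial with at least 80% power for 25 points, when the realised figure may be nearer 70 to 75%. The Discussion itself remarks that few mHealth trials have been adequately powered, so readers will look at this figure.

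**Working it through.** **Inputs from the article.** n = 60 per arm, two-sided α = 0.05 (z = 1.960), difference d = 0.25, simple chi-square test. **Assumption.** The control rate p₁ at 6 months is 30 to 40%, the article's baseline range, since it gives no other rate. Then p₂ = p₁ + 0.25.

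**Step 1: reproduce the stated figure.** With p̄ = (p₁ + p₂)/2 and S = p₁(1−p₁) + p₂(1−p₂), the pooled-variance formula is

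power = Φ{[d√n − 1.960·√(2p̄(1−p̄))] / √S}.

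- 30% vs 55%: d√n = 0.25 × 7.746 = 1.936; √(2 × 0.425 × 0.575) = 0.699; √S = √0.4575 = 0.676. Power = Φ[(1.936 − 1.370)/0.676] = Φ(0.837) = 79.9%.
- 35% vs 60%: √(2 × 0.475 × 0.525) = 0.706; √S = √0.4675 = 0.684. Power = Φ[(1.936 − 1.384)/0.684] = Φ(0.808) = 79.0%.
- 40% vs 65%: the same as 35% vs 60% by symmetry, 79.0%.

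The unpooled formula is Φ[d/√(S/n) − 1.960]. It gives Φ(2.863 − 1.960) = 81.7% at a control rate of 30%, and Φ(2.832 − 1.960) = 80.8% at 35% and 40%. Exact binomial enumeration of the Pearson chi-square test gives 80.6%, 80.3% and 80.3%. The claim of 80% reproduces at full follow-up.

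**Step 2: is there any reserve?** The pooled formula needs [1.960·√(2p̄(1−p̄)) + 0.842·√S]²/d² per arm. This is 60.2 at a control rate of 30% and 61.4 at 35% or 40%, so 61 to 62 after rounding up. The unpooled formula needs 58 to 59. The planned 60 is thus the number required for analysis, with nothing added for loss.

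**Step 3: power with equal loss in both arms.** The loss rates are assumptions. Ranges cover control rates of 30, 35 and 40%.

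| Loss | Analysed per arm | Pooled | Exact chi-square | Unpooled |
|---|---|---|---|---|
| none | 60 | 79.0–79.9% | 80.3–80.6% | 80.8–81.7% |
| 1 per arm | 59 | 78.4–79.2% | 79.2–79.5% | 80.2–81.0% |
| 2 per arm | 58 | 77.6–78.5% | 78.0–78.4% | 79.5–80.4% |
| 5% | 57 | 76.9–77.8% | 76.8–77.4% | 78.8–79.7% |
| 10% | 54 | 74.6–75.5% | 73.0–74.8% | 76.6–77.5% |
| 15% | 51 | 72.1–73.0% | 74.9–75.1% | 74.2–75.2% |
| 20% | 48 | 69.5–70.4% | 70.3–70.8% | 71.7–72.6% |

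Exact power does not fall smoothly with n, because the test is discrete; hence its rise from 54 to 51 per arm. The pooled column is the one to quote for a trend. At 5% loss all three methods are below 80% over the whole range.

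**Step 4: loss counted as non-adherence.** With all 60 per arm kept and equal loss ℓ, both rates are multiplied by (1−ℓ), so the difference shrinks to 0.25(1−ℓ). Pooled power at control rates of 30/35/40% is 72.3/70.7/69.9% for ℓ = 10% and 64.1/61.9/60.5% for ℓ = 20%.

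**Step 5: does using a baseline rate flatter the calculation?** For a fixed 25-point difference, power is lowest when p̄ = 0.5, that is at a control rate of 37.5%, where pooled power is 78.9%. It is 81.6% at a control rate of 25% or 50%, and 84.1% at 20%. The 30 to 40% range is already close to the least favourable.

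**The case against.** **The figure is right as computed.** This stands. At 60 analysed per arm the planned test has about 80% power, and only the pooled approximation falls marginally short. A reader might infer that the sample size arithmetic is wrong; it is not.

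**A condensed article need not state a dropout allowance.** True, and the absence of one, or of a missing-data rule, is not the point here. The point is a printed power tied to a printed number randomised. An allowance recorded elsewhere would not reconcile them, because a sample already enlarged for loss would show surplus power at 60 per arm, and over 30 to 40% there is none. A control rate of 20% would need 54 per arm, and 54/0.9 = 60 would then cover 10% loss, but that rate lies outside the article's own range.

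**A reader might infer that any single loss breaks the claim.** That is too strong. The unpooled formula tolerates one loss per arm across the range, and two at a control rate of 30%. Exact power at 30% is also 80.2% when two participants are lost from the intervention arm alone. The shortfall at 5% loss is at most about 3 points.

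**A reader might infer that improvement among controls by 6 months weakens the trial further.** At a fixed 25-point difference it does not, as Step 5 shows. What remains is labelling: the rate is described as a baseline rate, while the powered comparison is at 6 months.

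**Other analyses.** Statistical analyses names a simple chi-square test for the main effect. Power under a more conservative test is therefore not relevant, and the adjusted regression cannot be used to rescue the figure, since it is not the main test and the article gives no baseline-to-outcome correlation.

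**Conclusion.** The concern holds in a limited form. The stated power is correct only if essentially all 120 randomised participants are assessed at 6 months, because 60 per arm is the number needed for analysis. Pooled-formula power is about 77–78% at 5% loss, 75% at 10%, 72–73% at 15% and 70% at 20%. Counting the lost as non-adherent lowers it to about 70–72% at 10% and 60–64% at 20%.

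This rests on three assumptions: a 6-month control rate of 30 to 40%, a true difference of exactly 25 points, and equal loss in both arms. The loss rates are illustrative, so the article does not support a statement that the trial will be underpowered by any particular amount. Severity is moderate: a power figure to restate, with no defect in the design or the test.

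**What to change.** Replace the power sentence in Sample size with wording such as: *Sixty participants per group analysed at 6 months give about 80% power, at a two-sided 5% level, to detect an absolute difference of 25 percentage points; with 10% and 20% loss to follow-up, power is about 75% and 70%.* Add that 30 to 40% is used as the assumed control rate at 6 months and that, for a fixed 25-point difference, this range is close to the least favourable.

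The cost is one slightly less favourable figure and no added patients. Keeping 80% by the pooled formula at 10% loss would instead take 2 × 61/0.9 = 136 to 2 × 62/0.9 = 138 randomised. That is not asked for here, since recruitment is open and an accurate statement of power is enough.

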### Randomisation and blinding

Following baseline data collection, eligible and consented participants will be randomised to either the intervention group or the control group in a 1:1 ratio. The randomisation sequence will be generated by using a computer program in blocks of six and will be overseen by the project statistician and unavailable to outcome assessors. Randomisation will be stratified according to smoking status (smoker vs. nonsmoker) to help balance baseline health behaviour scores. Allocation will be concealed in consecutively numbered, opaque sealed envelopes. Owing to the nature of the intervention, participants will be aware of the group to which they have been assigned; however, at follow-up, outcome assessors will be blinded to the treatment allocation.

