## Trial status

The trial is currently open for recruitment.

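### A single fixed block of six, published during recruitment, could let staff who track allocations within a stratum know up to about a quarter of the remaining ones in advance

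*Protocol article*

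**What the plan says.** The section Randomisation and blinding fixes the scheme:

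- Block length: "The randomisation sequence will be generated by using a computer program in blocks of six".
- Ratio: participants are "randomised to either the intervention group or the control group in a 1:1 ratio", so each block holds three of each arm.
- Strata: "Randomisation will be stratified according to smoking status (smoker vs. nonsmoker) to help balance baseline health behaviour scores". Hospital is not named as a stratification factor.
- Concealment: "Allocation will be concealed in consecutively numbered, opaque sealed envelopes".
- Access: the sequence is "overseen by the project statistician and unavailable to outcome assessors". Staff who screen, consent and enrol are not mentioned.
- Blinding: "participants will be aware of the group to which they have been assigned"; assessors are blinded at follow-up.

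Outcome assessments gives the timing: "The baseline assessment concludes with randomisation and assignment of participants to the respective study groups". Study sample and recruitment adds that patients get an information sheet in hospital, that consent is taken at the baseline assessment, and that assessments may be held in hospital, a community clinic or the home. Trial status reports: "The trial is currently open for recruitment".

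**The concern.** Sealed envelopes hide the next card. They do not hide what the earlier cards in the same block imply once the block length is known. Here the length is constant and public, there are only two strata, and past allocations are not secret in principle: participants know their arm, intervention participants receive a pedometer and a telephone voucher, and the study team answers their texts. The stated protection covers outcome assessors, who need blinding. Concealment has to protect against foreknowledge among those who recruit.

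There is also room to act on foreknowledge. Consent and baseline data come before the envelope is opened, but whom to pursue after the information sheet, and when to hold the baseline visit, are decided earlier. If a likely intervention slot attracted more motivated patients, the primary outcome would be exposed directly, because all four components of the behaviour score are self-reported and the main test is an unadjusted χ² comparison.

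**Working it through.** The article gives no predictability figure to reproduce. Its only design calculation is the power statement, which does not bear on this point.

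**Inputs from Randomisation and blinding:** block length 6, ratio 1:1 (m = 3 per arm), two strata. **From Sample size:** N = 120. **Assumed:** 5% to 30% smokers, and the ways of sharing envelopes set out below.

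**1. Certain allocations in a complete block.** There are C(6,3) = 20 equally likely arrangements. An allocation is certain once one arm is used up.
- Position 4 is certain if the first three are all one arm: 2/20 = 0.10.
- Position 5 is certain if the last two are the same arm: (4 + 4)/20 = 0.40.
- Position 6 is always certain: 1.00.

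Sum: 0.10 + 0.40 + 1.00 = 1.5 of 6, or 25%. The closed form 1/(m + 1) = 1/4 agrees.

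**2. Best guess (the arm that is behind; a coin toss when level).** Expected correct guesses per block are m + ½[2^(2m)/C(2m,m) − 1] = 3 + ½(64/20 − 1) = 4.1. That is 4.1/6 = 68.3%, against 50% by chance.

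**3. Incomplete last blocks.** Simulating 120 participants with 5% to 30% smokers gives about 24% certain with one sequence per stratum, and about 23% with a separate sequence for each hospital.

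**4. Partial sight of past allocations.** Suppose two recruiters share a sequence, each handles a random half and sees only that half. An allocation is then certain only if the recruiter personally saw all three cards of the used-up arm: 0.25 × (1/2)³ = 3.1%. Simulation gives 3.0%.

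**5. Effect of varying the block size.** The observer is assumed to see all past allocations and to know the set of sizes but not their order (simulated, 60 allocations per sequence).

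| Sizes | Certain | Best guess correct |
|---|---|---|
| 6 fixed | 25% | 68% |
| 4, 6 | 6% | 69% |
| 2, 4, 6 | 4% | 70% |
| 4, 6, 8 | 2% | 68% |

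The last column hardly moves because guessing the lagging arm needs only a running tally, not the block sizes. For sizes 4 and 6, blocks of four give 2.83 correct guesses, so (2.83 + 4.1)/10 = 69%.

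**The case against.** The strongest reply is that 25% is a ceiling. It needs one person to know every earlier allocation in a stratum and where each block starts. The article does not say who enrols, who opens envelopes, or how envelopes are divided between the two hospitals. A condensed article may leave such handling to the full protocol, so silence on it is not in itself a fault. All of this stands. A reader might infer that recruiters can foresee a quarter of allocations outright; the document does not support that.

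Nor does it support the inference that 0.25 × 120 = 30 participants were foreseeable. Publication can matter only for those enrolled afterwards. The article does not say how many remained, or that staff knew the block length from the start.

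A reader might also infer that nothing in the analysis addresses such bias. In fact, Statistical analyses plans regression adjusted for baseline confounders, self-efficacy is a listed outcome with baseline collection before allocation, and stratification balances smoking. Measured imbalance could therefore be seen and partly adjusted for. Unmeasured motivation could not, and the χ² test is unadjusted.

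Finally, varying the block size does not lower best-guess success, and Study intervention rules out design changes once recruitment begins. Both points stand and shape the remedy. They do not remove the concern, because the article positively states a predictable scheme during recruitment; it does not merely leave out detail.

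**Conclusion.** The point holds as a conditional risk. With full tracking within a smoking stratum and knowledge of block starts, up to about a quarter of the remaining allocations could be known in advance: 25% in complete blocks, and about 23% to 24% allowing for incomplete ones. If two recruiters share a sequence and each sees half, the share is about 3%. That figure is an illustration, not a floor, since staff who see fewer past allocations would know less.

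Nothing in the document shows that any allocation was foreseen or any enrolment steered. The resulting bias in the primary comparison cannot be sized from the documents. Adjusted regression may reduce it but cannot be relied on to remove it, and selection at enrolment cannot be undone once recruitment has closed.

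**What to change.** For envelopes not yet used, have the project statistician reissue the sequence within each smoking stratum, with randomly varying block sizes that are not disclosed until recruitment ends. Amend Randomisation and blinding so that the sequence and block sizes are unavailable to everyone who screens, enrols or assesses, without printing the new sizes.

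Non-disclosure matters as much as varying the size. If the set of sizes became known, certain allocations would still fall from 25% to about 2% to 6%, but best-guess success would stay near 68% to 70%. That part is reduced only by also keeping the tally of past allocations from those who enrol, as far as practicable.

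The cost is one new list and one set of envelopes. Ratio, strata and analysis are unchanged. Balance between arms becomes slightly looser: an abandoned part-used block can leave a difference of at most three in its stratum. The change is a mid-recruitment amendment. It must be reported to the ethics committees, as Ethical approval provides for, and expressly reconciled with the statement in Study intervention that the design will not change once recruitment begins.
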